## Background

Dementia, which remains incurable using existing technologies, has become a global health crisis. Recently, clinical research and basic research have focused on the preclinical stage of dementia—mild cognitive impairment (MCI) (1). MCI denotes problems with memory, attention, or other cognition, which are greater than expected for healthy aging but insufficient to interfere with daily activities (2). The clinical outcomes of MCI may remain stable, progress to dementia, or return to neurological integrity. The annual conversion rates from MCI to dementia are estimated from 10 to 59.4%, whereas 14.4 to 55.6% of those with MCI revert to normal cognition (NC) (3). The higher rates of MCI reversion emphasize the importance of early prevention and treatment at the MCI stage to forestall further cognitive decline.

Drug treatments resulted in no effect in any of the MCI studies (*N* = 53,693 patients, 95% CI: 0.000 to 0.005) (4), meaning that recent efforts have focused on non-pharmacological cognitive dysfunction management strategies, which have been proved promising for delaying cognitive decline, including physical exercise, cognitive training, musical therapy, mental/social activity, eating habits, and multi-domain interventions (5, 6).

In fact, older adults with MCI have poor compliance with participation in these cognitive dysfunction management strategies, with an average non-adherence rate of ~25% (7). There are many factors that influence compliance, including patients' lack of understanding of their disease, lack of social support, low sense of self-efficacy, and financial constraints (8). A promising intervention to improve compliance and educational strategies would help participants understand health information, and this may be essential to help individuals generate the motivations, beliefs and improve their overall compliance behavior (7, 9).

Health education can improve individual's level of disease knowledge, and it is an essential component of chronic disease management strategies. Health education helps individuals to understand the essence of disease management and encourages individuals to participate in their own disease management (10, 11). Nevertheless, previous studies have shown that older adults in the community still lack knowledge about the cause, diagnosis, and treatment of cognitive impairment. A total of 55.5% of community-dwelling older adults did not perceive themselves as very knowledgeable about dementia; more than 65% thought dementia was caused by healthy aging (12, 13). Meanwhile, older adults with MCI had lower scores with knowledge of dementia than those with normal cognition, and the scores would decrease as cognitive impairment worsened gradually (14). In addition, some limitations also occurred in health education activities aimed at the population with cognitive dysfunction, educators placing more emphasis on patients with dementia and their caregiver rather than those with MCI; the lack of health education programs for older adults with MCI in the community setting (15); and the failure to assess the extent of behavioral change caused by a health education (16). Anghel et al. found that better compliance behaviors were related to increased knowledge of the disease (17). Nevertheless, whether health education can improve the compliance of participation in cognitive dysfunction management for older adults with MCI is not clear.

The trans-theoretical model (TTM) is an integrative model of behavior change that has been applied successfully to improve compliance, self-management, and health behavior in older adults and patients with chronic diseases (18–20). The effectiveness of behavioral changes may increase, framing them with the TTM (18). TTM emphasizes behavior change as a process rather than a single event, which posits that individuals move through five stages of adoption health-promoting behaviors (i.e., pre-contemplation, contemplation, preparation, action, and maintenance) (21). Nevertheless, no education program based on TTM has been proven to promote behavior change and other cognition-related health outcomes on older adults with MCI.

To address this gap, we developed a TTM-based health education program, which was targeted to improve the disease knowledge and the compliance of participation in cognitive dysfunction management for older adults with MCI.

Our study seeks to answer two primary questions:

(1) What are the impacts of a TTM-based health education program on older adults with MCI? We hypothesize that this program would positively affect the level of compliance of participation in cognitive dysfunction management, disease knowledge, and other cognition-related health outcomes (general cognitive function, sleep quality, depression symptoms, apathy symptoms) for older adults with MCI compared to the control group.

(2) Is it feasible to use the TTM-based health education program for recruitment and compliance in the community setting? We hypothesize that older adults with MCI would be unlikely to refuse to participate in this program and would have high compliance, and no adverse events would occur during the intervention.

## Materials and Methods

### Study Design and Participants

This study is a randomized controlled trial (RCT, Clinical Trials.gov number: ChiCTR1900 028351) with a 3-month follow up. This protocol has been approved by an independent ethics committee (Third People's Hospital of Huzhou, Zhejiang Province). It will be conducted in accordance with the ethical principles of the Declaration of Helsinki. The participants will be recruited from the community's health care center in Huzhou, Zhejiang Province, China. This program will consist of two arms: the intervention group (TTM-based health education program) and the control group (standard health education).

Our staff will distribute recruitment leaflets at community health care centers and local senior centers. Local health care providers will also help to make referrals to our study. Individuals who show interest will be invited for an in-person interview to screen for eligibility by three trained staff and a trained neurologist-psychiatrist will examine the potential participants to provide the final diagnosis of MCI. In the first round of eligibility assessments, potential participants complaining of memory impairment will be recruited. The second round of eligibility assessments will include demographic data, sensory function evaluation, cognitive function, and functional evaluation of activities of daily and medical history.

Participants will be eligible for the trial if they are 60 years of age or older with Petersen criteria for MCI (22). Participants who have severe physical disorders or mental disorders at present, or who have unfortunate events during the trial or follow-up period will not continue to receive the health education program and will be withdrawn from the study. Detailed inclusion and exclusion criteria are listed in Table 1. All participants will be fully informed of the program protocol, and only those who sign the informed consent before baseline will be included in this study. They will receive a gift for the completion of each session of the TTM-based health education program.

**Table 1 T1:** Inclusion criteria and exclusion criteria.

**Inclusion criteria**	**Exclusion criteria**
■ Aged 60 years or over ■ Meet diagnostic criteria of MCI proposed by Petersen (22) • Chief complaint of memory impairment confirmed by self-report/relatives; • Objective cognitive impairment inconsistent with age and education Montreal Cognitive Assessment-Basic (MoCA-B) scores 18 for those with elementary education level, scores 21 for those with secondary education level, scores 23 for those with tertiary education level (23); • Preserved global cognitive function as evidenced by Mini-mental State Examination (MMSE) score ≥24 (24), and absence of dementia [diagnosis by a psychiatrist according to DSM-V (25)]; • Intact Activities of Daily Living (ADL) [ADL score was ≤ 16 (26)] ■ Absence of self-reported visual or auditory impairmen ■ Capacity to provide written informed consent ■ Willingness to participate in the entirety of the study	■ History of severe disease (e.g., severe cardiovascular and cerebrovascular diseases, cancer and other severe physical disease, psychiatric disorders (neurodevelopmental disorders, schizophrenia spectrum, major depression disorder, obsessive-compulsive and related disorders and other major psychotic disorders), terminal illness) ■ Serious events occurring during the intervention period (e.g., acute stroke, fall) ■ Lost to follow-up ■ Participation in another training related to cognitive function within 1 year

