### Randomization, Allocation Concealment, and Blinding

After completing the screening, eligible participants will be allocated randomly to one of two groups: TTM-based health education program group (intervention group) or standard health education group (control group) in a ratio of 1:1 using a computer-generated random number list. The random allocation sequence will be sealed in opaque envelopes by a staff member who will be not involved in study intervention, screening assessments, data collection, or data analysis. Participants will be informed that they will learn facts and management strategies about MCI, and that they will be blinded as to whether they receive health education based on TTM or standard health education. The data collectors and the data analyst will be blinded to group allocations.

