#### Data Collection

Before randomized allocation, the baseline data (T0) will be collected at a community health care center by the staff blinded to group allocation, including socio-demographic profile, primary outcomes and secondary outcomes; primary outcomes, and secondary outcomes will be measured again at the end of the intervention (T1) and 3 months after intervention (T2). Table 2 shows the assessment and timeline of the study.

**Table 2 T2:** Summary of study assessments and time-lines.

	**Questionnaire items**	**Time point**				
		**Baseline**	**Randomized allocation**	**Intervention**	**Post intervention**	**Follow-up 3 months**
		**T0**			**T1**	**T2**
Enrollment						
Eligibility screening						
Informed consent						
Screening	**General information**					
	Demographic information	✓				

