### Statistical Analysis

Data collection will be conducted in a single room and kept in a password protected computer folder. Collected data will be encoded in Excel and double-checked. Data processing and statistical analysis will be conducted using SPSS 22.0. Descriptive statistics will summarize demographic data and observable variables using frequencies and percentages for categorical variables, means ± standard deviations for continuous variables. We will employ exploratory analysis (normality testing and distribution curves) to examine the distribution of data. The proportionality of baseline data for both groups will be compared using the non-parametric Wilcoxon test, the Chi–square test, and the *T*-test. A 2 (group) × 3 (time) ANOVA will be used to determine the effect of the group factors, the intervention group and control group differences within-group over time, and interaction effects. Simple effect analysis will be added when there is an interaction between group factors and time factors. The intention-to-treat principle will follow data analysis. A two-tail *P*-value of < 0.05 will be considered statistically significant.

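### Table 1 lists two events that can only follow randomisation as exclusion criteria, and the text withdraws participants with events from the study, in conflict with the stated intention-to-treat principle

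*Protocol article*

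**What the plan says.** Four places in the protocol article bear on this.

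- **Eligibility (Study Design and Participants, Table 1).** The text says "Detailed inclusion and exclusion criteria are listed in Table 1". The exclusion column of that table includes "Serious events occurring during the intervention period (e.g., acute stroke, fall) ■ Lost to follow-up".
- **Withdrawal (Study Design and Participants, text).** Among those covered are participants "who have unfortunate events during the trial or follow-up period". They "will not continue to receive the health education program and will be withdrawn from the study".
- **Order of events.** Under Randomization, Allocation Concealment, and Blinding: "After completing the screening, eligible participants will be allocated randomly to one of two groups". Under Data Collection: "Before randomized allocation, the baseline data (T0) will be collected". Outcomes are measured again at the end of the intervention (T1) and 3 months after it (T2).
- **Analysis (Statistical Analysis).** "The intention-to-treat principle will follow data analysis". The comparison is a 2 (group) × 3 (time) ANOVA.

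No sentence limits the two Table 1 items to stopping the sessions, and none says that a participant who meets one of them stays in the analysis.

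**The concern.** An exclusion criterion decides who enters a trial and should be settled before allocation. A criterion that can be met only afterwards cannot screen anyone out; it can only take out someone already randomised. Intention-to-treat means the reverse: everyone randomised is analysed in the arm to which they were allocated. The eligibility and withdrawal wording therefore pulls against the analysis statement.

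At stake is the randomised comparison on both primary outcomes, compliance and MCI knowledge. The arms differ in ways that could affect who stays. The intervention arm has weekly sessions of 45–60 minutes and the control arm has 45-minute sessions every two weeks, delivered at different sites. If removal depends on arm and on how participants are doing, the groups that remain are no longer those that randomisation made comparable. Outcomes that a withdrawal rule stops collecting cannot be recovered at the analysis stage.

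**Working it through.** **1. Can either item act before randomisation?** Screening and T0 come first, then allocation, then the intervention, then T1 and T2. A serious event during the intervention period falls after allocation by definition. Loss to follow-up concerns T1 or T2, which also come after it. So neither item can affect entry; each can act only on a randomised participant.

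**2. What happens to that participant?** The withdrawal sentence states two consequences: the programme stops, and the participant leaves the study. The first concerns treatment. The second, on its natural reading, ends T1 and T2 data collection. The scope also differs: Table 1 limits serious events to the intervention period, while the text covers the trial or follow-up period.

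**3. What data would be lost through the rule itself?** Two groups:
- participants with an event who could still be assessed at T1 and T2;
- participants assessed at T1 and lost before T2, whose existing data would be discarded if they are treated as excluded.

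Anyone who cannot be reached has missing later data whatever Table 1 says. The documents give no number for either group.

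**4. Planning figures, for scale (Sample Size).** Inputs: d = 0.684, α = 0.05 two-sided, power 0.95 (printed as β), 15% dropout, 1:1 allocation.
- A two-sided independent t-test (noncentral t) gives 56.5 per arm, rounded up to 57, so 2 × 57 = 114. This reproduces the plan's figure.
- 114 × 1.15 = 131.1, rounded up to 132. This also reproduces.
- Planned dropout: 0.15 × 132 = 19.8, about 20, leaving about 112.
- Power at d = 0.684 is about 0.974 with 132 and about 0.948 with 112.

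Lost power is therefore not the main issue, even if all planned dropout is counted.

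**5. Illustration of bias (assumed inputs, not in the documents).** In one arm, the mean of those retained differs from the mean of all randomised by (removal rate) × (gap between retained and removed). With the same gap in both arms, the bias in the difference between arms is

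bias = gap × (removal rate in one arm − removal rate in the other).

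Assume removal of 20% and 10%, which averages to the planned 15%, and a gap of 0.5 to 1.0 SD:
- 0.5 × 0.10 = 0.05 SD, and 0.05 / 0.684 = 7% of the design effect;
- 1.0 × 0.10 = 0.10 SD, and 0.10 / 0.684 = 15% of the design effect.

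This attributes all dropout to the rule. Only the part described in step 3 is attributable to it, so for the same gap and split the bias shrinks in proportion. The direction is not known. With equal removal rates and equal gaps, the bias by this formula is zero.

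**The case against.** The strongest reply is that these are withdrawal criteria placed in the wrong column. The surrounding text uses the language of withdrawal, and the only sentence about the analysis promises intention-to-treat. On that reading, data collected before withdrawal could still be analysed by allocated arm, and how that is done may be set out in a fuller protocol or SAP that is not shown.

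Part of this stands. No sentence says that these participants are removed from the analysis; a reader might infer it from the table heading together with the withdrawal rule, but it remains an inference. The passages are in tension and need reconciling. The absence of a missing-data method is not the complaint. What does not fall away is that Table 1 calls these items exclusions, and that withdrawal from the study, taken literally, stops outcome collection. An SAP cannot restore outcomes that were never collected.

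Three further inferences are tempting and are not supported:
- **That the rule removes 20 participants.** That is the total planned dropout. Sample Size does not split it by cause, and deleting the loss-to-follow-up item would not bring back people who cannot be reached.
- **That the safety hypothesis, "no adverse events would occur during the intervention", becomes self-fulfilling.** The Control Group section has staff ask about adverse effects at each session, and nothing says that an event leading to withdrawal goes uncounted. Reporting events for everyone randomised is a sensible safeguard, not the repair of a shown defect.
- **That gifts drive unequal loss.** Session gifts are stated only for the TTM programme, but Retention Strategies also lists a gift for baseline and follow-up interviews, without limiting it to one arm.

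**Conclusion.** The concern holds as a conflict within the protocol article. Two events that can only follow randomisation are listed as exclusion criteria, and participants with events are withdrawn from the study, while the analysis is said to follow intention-to-treat. Applied as written, these rules would drop randomised participants or end their T1 and T2 data collection. That could bias the primary comparisons if removal differs by arm; the documents do not show that it will.

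The size cannot be derived from the documents. About 20 of 132 is an upper bound at planning level, and the 0.05 to 0.10 SD range is an illustration that rests on assumed removal rates and an assumed common gap. The conflict in the wording depends on none of these figures.

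**What to change.** - Remove serious events during the intervention and loss to follow-up from the exclusion criteria, leaving only conditions that can be judged before allocation.
- Reconcile Table 1 and the withdrawal sentence with Statistical Analysis by separating stopping the sessions from leaving the study, and align the period that each covers.
- State that all randomised participants are analysed in their allocated arm, using all data collected.
- State that participants who stop sessions are still invited to T1 and T2 unless they withdraw consent.
- Report serious events by arm for all randomised participants.

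Whether a participant stops the sessions remains the sponsor's clinical rule and is not touched here.

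The cost is a small amendment to the withdrawal wording and a few additional T1 and T2 assessments. Retention Strategies does not explicitly provide for visits by withdrawn participants (its contact attempts are aimed at completing the intervention), so these visits should be written in. The article describes the study as ongoing; the follow-up part of the fix helps only participants whose T1 or T2 assessment is still to come.

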### Sample Size

Based on our pilot study, Cohen's *d* = 0.684, effect size =0.324. Cohen's d and the effect sizes were calculated for between-group differences of means of the level compliance of participation in cognitive dysfunction management using an independent-groups pre-test and post-test design (IGPP). Sample size estimation was conducted using statistical software G^*^power. The analysis, with an independent *t*-test using β = 0.95 and α = 0.05, requires a total sample size of 114 participants. Considering a 15% dropout rate, our total sample size comes to 132 participants (66 cases for both the intervention and control groups).

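### At the stated 15% dropout, 132 participants leave about 112, not the required 114; power is essentially unchanged, and the value labelled β is the power

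*Protocol article*

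**What the plan says.** The Sample Size section takes its effect size from a pilot study: "Based on our pilot study, Cohen's *d* = 0.684, effect size =0.324". It describes the calculation as run in G*Power "with an independent *t*-test using β = 0.95 and α = 0.05", and reports a requirement of 114 participants in total. It then adds the allowance for loss: "Considering a 15% dropout rate, our total sample size comes to 132 participants", that is, 66 per arm. It does not print the formula that leads from 114 to 132, and it gives no power value apart from the 0.95 labelled β.

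Two further inputs come from other sections. Randomization, Allocation Concealment, and Blinding sets allocation "in a ratio of 1:1 using a computer-generated random number list". Statistical Analysis fixes the sidedness of testing: "A two-tail *P*-value of < 0.05 will be considered statistically significant".

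**The concern.** A dropout allowance has one job: after the assumed loss, the number the power calculation requires should still be there. Dropout is a fraction of those enrolled, so the enrolled number times 0.85 should be at least 114. With 132 enrolled it is not. Adding 15% to the required number, instead of dividing by the retained fraction, is a common slip, and 132 has the size that this slip would produce.

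The notation is a second, lesser matter. β conventionally denotes the type II error rate, so "using β = 0.95 and α = 0.05" read literally describes a trial with 5% power.

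What is at stake is whether the sample-size statement is correct and can be reproduced from its own figures. The trial's ability to detect the planned effect is hardly touched.

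**Working it through.** **Inputs.** From Sample Size: d = 0.684, α = 0.05, the value 0.95, required total 114, dropout 15%, enrolled total 132 (66 per arm). From Randomization: 1:1 allocation. From Statistical Analysis: two-sided testing.

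**Step 1: reproduce 114.** For a two-sample t-test with n per arm, the degrees of freedom are 2n − 2 and the noncentrality is d × √(n/2). Power follows from the noncentral t distribution. With d = 0.684 and two-sided α = 0.05:

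| n per arm | Total | Power |
|---|---|---|
| 56 | 112 | 94.82% |
| 57 | 114 | 95.16% |
| 66 | 132 | 97.38% |

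The smallest n that reaches 95% power is 57 per arm, or 114 in total, which is exactly the article's figure. A one-sided test would need 47 per arm (94). Two-sided power of 90% would need 46 per arm (92). So 0.95 entered the calculation as power, and β was 0.05.

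**Step 2: the second effect size.** The 0.324 is the correlation form of the same effect: d/√(d² + 4) = 0.684/√(0.468 + 4) = 0.324. It is not a competing value of d; as a d it would need 498 participants at 95% power, not 114.

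**Step 3: find how 132 arises.**

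- Multiplying: 114 × 1.15 = 131.1, which rounds up to 132 in equal arms. Per arm, 57 × 1.15 = 65.55, which rounds up to 66. Both match the article.
- Dividing: 114/0.85 = 134.1, or 135 in total. Per arm, 57/0.85 = 67.06, which rounds up to 68, or 136 in equal arms. Neither gives 132.

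**Step 4: check what 132 leaves.**

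- At 15% dropout: 132 × 0.85 = 112.2, or 66 × 0.85 = 56.1 per arm.
- Shortfall against 114: 114 − 112.2 = 1.8, about 2 participants.
- Largest dropout that still leaves 114: (132 − 114)/132 = 18/132 = 13.6%.
- Power at 56 per arm, from Step 1: 94.8%, which is 0.2 percentage points under 95% and between 0.3 and 0.4 points under the 95.16% reached at 57 per arm.

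**The case against.** The strongest objection is materiality. Power of 94.8% equals 95% to the two decimals the article prints. The difference is also far smaller than the uncertainty in the inputs: with 56 per arm, power returns to about 95.0% if d is 0.687 instead of 0.684, while a d of 0.65 would lower power to 93.1% even with the full 57 per arm. The d comes from a pilot whose size and precision are not given, and the 15% is itself a planning guess. All of this stands. It keeps the point minor and rules out any claim that the design fails.

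A reader might infer more: that the trial does not deliver its planned power, or, from the β label, that it was planned with 5% power. The documents support neither. Step 1 shows that power was set at 95%, and the dropout slip leaves it essentially there.

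It is also fair to say that the multiplication by 1.15 is inferred, since no formula is printed. It should be described as consistent with the figures and not as stated. The shortfall does not depend on it, because 132 × 0.85 is below 114 however 132 was reached.

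Two defences do not hold. That an article condenses a longer protocol excuses omissions, but here the printed figures disagree with one another. The intention-to-treat statement in Statistical Analysis does not restore the 114 either, since the article describes no method for missing outcomes.

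**Conclusion.** The point holds as a minor correction. At the stated 15% dropout, 132 enrolled leave about 112 evaluable participants, about 2 fewer than the 114 the article requires. Dividing by 0.85 would have given 135 in total, or 136 in equal arms, which is 3 or 4 more than planned. Power at the reduced number is 94.8%, so the trial is not shown to be underpowered. The β label is a secondary notation error with no effect on the sample size.

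This rests on three readings: dropout is a fraction of those enrolled, it falls equally on both arms, and participants who drop out contribute no outcome to the t-test comparison. The arithmetic is otherwise certain, since 114 reproduces exactly.

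**What to change.** Keep 132 and correct the statement in Sample Size along these lines: *1 − β = 0.95, two-sided α = 0.05, d = 0.684; 132 randomised participants retain the required 114 for dropout up to 13.6%; at 15% dropout about 112 evaluable participants remain, giving about 94.8% power.*

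The cost is a corrected sentence and a marginally less favourable stated figure. Trial Status says recruitment is under way, and a shortfall of this size gives no reason to enlarge the trial; nothing in conduct, analysis or timeline changes.
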